### 2.6. tDCS Treatment, Simulation and Blinding

#### 2.6.1. tDCS Device

Participants will undergo an intervention tDCS treatment using a battery-driven and portable device (Neurophet innk, Neurophet, Seoul, Republic of Korea), programmed to deliver either active or sham tDCS. The device delivers 2.0 mA (with 30 s for ramping up and ramping down; Figure 2) of the direct current through the two sponge-coated electrodes (electrode size: 5 × 5 cm^2^). The tDCS device used in this study can check the impedance values occurring in patient’s skin, in real time, during all tDCS sessions. If an impedance above 13 kOhm occurs, the stimulation is stopped, and the medical device investigator confirms the patient’s condition and skin. This may reduce the adverse events that may occur on the patient’s skin, due to the increased impedance. In the sham-tDCS condition, the device delivers 120 s of the current, including 30 s for ramping at the beginning and end of each session, to maintain the blinding procedure. The tDCS treatment was performed 10 times over a total of 2 weeks, and sham-tDCS was also applied 10 times with sham stimulation for 2 weeks. Following this duration, both opt-tDCS and con-tDCS groups, but not the sham-tDCS group, will receive the opportunity to provide additional written consent for an extension study; if the participants give consent, the extension study will be conducted for two additional weeks. During the 2 or 4 weeks of intervention, if there was a usual rehabilitation program that was being performed before participation in this study, the program and frequency could be continued without any changes. The detailed intervention methods regarding tDCS for each group, is as follows (Figure 3a). The representative figure which represents the difference between optimized tDCS and conventional tDCS simulation results in participant is Figure 3b.

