### 2.8. Primary Outcome

Upper limb functional changes will be evaluated by the FMA-UE scores, between the baseline and postintervention, at 2 weeks. The FMA-UE is a performance-based impairment index, including the motor function with a range of motion and sensation in patients with a stroke, and the results are represented as a numerical score with a maximum of 66 points [27,29].

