### 2.11. Statistical Analyses

The descriptive statistics (average, standard deviation, median, minimum, and maximum) are presented for each group for the change in the primary outcomes at 2 weeks, compared to the baseline (0 weeks), and the comparison of differences between the groups will be the repeated measures ANCOVA that considers time as a covariate. If statistically significant changes were confirmed in the comparison of the differences between the three groups, a repeated ANCOVA that considered the timing of the differences between the two groups (e.g., opt-tDCS and con-tDCS, opt-tDCS and sham-tDCS) was planned as a post hoc analysis. The results corresponding to the secondary outcomes will be presented as descriptive statistics (frequency, ratio) for each group, based on the change in score at 4 weeks, and the difference between the two groups, will be analyzed using the repeated measures ANCOVA, that considers time.

The primary outcome will be analyzed in the intention-to-treat population, and the safety outcomes will be analyzed in the per-protocol population. No protocol interim analysis is planned, and a total of 42 patients will be enrolled in this clinical trial over a total of 30 months. This sample will be able to evaluate the clinical applicability of the optimized tDCS treatment in the subacute to chronic stages of a stroke and aims to verify the trends in the intergroup differences and the changes to demonstrate the statistically significant differences in the upper limb function improvement between the two groups.

The outcome analysis of this trial will be largely divided into a safety set (SS) group, a full analysis set (FAS) group, and a per-protocol set (PP) group. The efficacy evaluation will analyze the PP group as the main analysis group and analyze the FAS group. If the results are different across the analysis groups, the results of each analysis method will be presented and analyzed to identify the reason. The safety assessment will be carried out in the SS group, and the significance level will be set at 0.05.

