**Figure 3 brainsci-12-01673-f003:**
[figure not shown]

[figure not shown]
(**a**) The intervention methods for the three groups. (**b**) Computational results of the optimized and conventional tDCS simulation.

**Table 1 brainsci-12-01673-t001:** Schedule of enrollment, interventions and assessment.

	Screening	Intervention			Outcomes	Extended Intervention		Outcomes
		Baseline						
Visit	V1	V2	V3~V6	V7~V11	V12	V13~V17	V18~V22	V23
ENROLLMENT								
Informed consent	V					V		
Eligibility screen	V	V						
Randomized allocation		V						
INTERVENTIONS								
Opt-tDCS Conv-tDCS Sham-tDCS		V	V	V		V	V	
ASSESSMENTS								
Baseline variables Vital signs Physical examination MRI scan MEPs EEG Functional examinations		V						
Outcome variables MRI scan MEPs EEG Functional examinations		V			V			V
Other variables Adverse events		V	V	V	V	V	V	V

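### Secondary outcomes are based on the 4-week change, which follows a voluntary extension closed to sham, so the stated analysis does not estimate the effect of the randomised 2-week treatment

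*Protocol article*

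**What the plan says.** All references are to the protocol article.

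- **Randomised treatment (2.6.1).** "The tDCS treatment was performed 10 times over a total of 2 weeks, and sham-tDCS was also applied 10 times". All three arms therefore have a 10-session, 2-week course.
- **Extension (2.6.1).** Afterwards "both opt-tDCS and con-tDCS groups, but not the sham-tDCS group, will receive the opportunity to provide additional written consent for an extension study", and "if the participants give consent, the extension study will be conducted for two additional weeks". The same section refers to "During the 2 or 4 weeks of intervention", so total exposure differs between patients.
- **Primary outcome (2.8).** FMA-UE change is read "between the baseline and postintervention, at 2 weeks", at the end of the randomised course.
- **Secondary outcomes (2.9 and 2.11).** These are MEPs, EEG, WMFT, BBT, ADLs and adverse events. Section 2.11 analyses them "based on the change in score at 4 weeks, and the difference between the two groups, will be analyzed using the repeated measures ANCOVA".
- **Visits (Table 1).** Outcome variables are collected at baseline (V2), at V12 after the 2-week intervention, and at V23 after the extended intervention. A further informed consent is marked at the start of the extension.

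**The concern.** The primary outcome is read when the only systematic difference between arms is the randomised treatment. The secondary outcomes are read two weeks later, when treatment received also depends on a second consent that sham patients are never asked to give. The Discussion says the trial aims to show benefit on ADL and neurophysiological measures as well as on upper limb function. ADLs, MEPs and EEG are secondary outcomes only, so that part of the aim rests on the 4-week analysis. The same measurements are already scheduled at V12, where the randomised comparison is intact.

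**Working it through.** **1. Which visit is 4 weeks?** Two weeks of treatment plus a two-week extension is 4 weeks. Table 1 has only two post-baseline outcome visits, V12 and V23, and V12 is the 2-week visit, so 4 weeks is V23. The abstract and 2.9 mention a 1-month follow-up and 2.9 points to Table 1, which shows no other later visit.

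**2. Exposure by V23.** Treatment visits V2-V11 number 10, matching the 10 sessions. V13-V22 number 10 more. An active-arm patient has therefore had 10 or 20 active sessions by V23, depending on consent. Under 2.6.1 a sham patient has had 10 sham sessions.

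**3. The two readings of V23 attendance.**

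| | Extension patients only | All randomised patients |
|---|---|---|
| Sham at V23 | 0 of 14 | up to 14 |
| Opt versus con | volunteers against volunteers | arms as randomised; compares 2 weeks plus an optional 2 more |
| Active versus sham | not possible | mixed 10/20 active sessions against 10 sham sessions |
| Effect of the 2-week course? | no | no |

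Under the second reading, with consent fraction c and full attendance by consenters, mean active sessions are 10 + 10c. That is 15 at c = 0.5 and 19 at c = 0.9.

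**4. Precision under the extension-only reading.** Inputs: 42 patients (2.10) allocated 1:1:1 (2.5), so 42/3 = 14 per arm. The consent rate is not given; I assume 50-90%. For a simple two-sample comparison in SD units, the 95% CI half-width is t(0.975, 2n − 2) × √(2/n).

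| Consent | n per active arm | Half-width (SD) |
|---|---|---|
| all 14 | 14 | 0.78 |
| 90% | 13 (12.6 rounded) | 0.81 |
| 70% | 10 (9.8 rounded) | 0.94 |
| 50% | 7 | 1.16 |

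These figures ignore dropout. With the article's 10% dropout, the starting point is 14 × 0.9 = 12.6. The difference detectable with 80% power (two-sided 0.05, normal approximation) is (1.960 + 0.842) × √(2/n). At 50% consent it rises from 1.06 to 1.50 SD starting from 14, and from 1.12 to 1.58 SD starting from 12.6.

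**5. Selection bias in opt minus con.** Assume no true difference and 60% consent in each arm. Consent follows a probit model with slope b on the 2-week change, and ρ is the correlation between the 2- and 4-week changes. Consenters then differ from their own arm at 4 weeks by ρ × b/√(1 + b²) × φ(z)/c, where z is the normal quantile of c. With b = 1 and c = 0.6 this is ρ × 0.707 × 0.644 = 0.455ρ. For ρ from 0.5 to 0.9:

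- same dependence in both arms: the shifts cancel and the bias is about 0;
- dependence in one arm only: 0.23 to 0.41 SD;
- opposite dependence in the two arms: 0.46 to 0.82 SD.

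A simulation with 400,000 patients per arm gave the same values. They illustrate the mechanism; nothing in the article fixes b, c or ρ.

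**The case against.** The strongest reply is that the article does not restrict V23 to extension patients, and a condensed article may leave attendance by arm to the full protocol. If everyone is assessed, opt and con were offered the same extension, so their V23 contrast is a valid randomised comparison of a treatment policy. That stands. It would be wrong to state as fact that the 4-week comparison is between self-selected patients. It does not rescue the contrast with sham, and the policy is not the 2-week treatment.

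Four stronger readings are tempting but not supported:

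- **That sham is dropped because 2.11 speaks of two groups.** The preceding post hoc sentence uses the same phrase for pairwise contrasts and gives opt versus sham as an example. The secondary sentence may carry that meaning.
- **That V12 is excluded.** A repeated measures model that considers time may well include V12. The stated basis is still the 4-week change, so the role of V12 needs saying.
- **That Table 1 contradicts 2.6.1 by giving sham an extension.** The entry "Opt-tDCS Conv-tDCS Sham-tDCS" is one cell with one shared row of marks, and the table was extracted by program. The marks cannot be assigned to an arm, and 2.6.1 excludes sham explicitly.
- **That the summaries are wrong because results are "presented as descriptive statistics (frequency, ratio) for each group".** Adverse events are among the secondary outcomes, and frequencies suit them. At most the wording is incomplete for the continuous measures.

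It is also fair that this is a phase 2 feasibility study with an exploratory sample size, and that only secondary outcomes are involved.

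**Conclusion.** The point holds. As written, the secondary analysis is anchored at a time when exposure depends on a voluntary extension closed to sham. Under either reading of V23 attendance, it does not estimate the effect of the randomised 2-week course. The text establishes this without any assumption about numbers.

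The size is uncertain. The loss of precision applies only if extension patients alone attend: from slight at 90% consent to a half-width about one and a half times as large at 50% (1.16/0.78 = 1.49). Bias in opt minus con needs consent to depend on response differently in the two arms, and could be nil. A reader might take the amount by which consenters exceed their own arm as the bias, but that amount cancels when both arms behave alike. The 2-week primary outcome is not affected.

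**What to change.** - **Section 2.11.** Make the baseline-to-V12 (2-week) change in all three randomised arms the main analysis of the secondary efficacy outcomes.
- **V23.** Report it separately as extension data, by number of sessions received, and descriptively. If all randomised patients are assessed at V23, a between-arm comparison may be kept, labelled as one of the treatment policy including the optional extension.
- **Section 2.6.1 and Table 1.** State consistently which arms attend V13-V23, and whether patients who decline the extension and sham patients are assessed at V23.

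The cost is wording and a table footnote. No new visit is needed, because the outcome variables are already scheduled at V12. The downside is that the 4-week comparison loses its main inferential status.

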## Abstract

Transcranial direct current stimulation (tDCS) has been shown to have the potential to improve the motor recovery of the affected upper limbs in patients with stroke, and recently, several optimized tDCS methods have been proposed to magnify its effectiveness. This study aims to determine the effectiveness of personalized tDCS using brain MRI-based electrical field simulation and optimization, to enhance motor recovery of the upper limbs in the patients. This trial is a double-blind, randomized controlled trial in the subacute to chronic rehabilitation phase. Forty-two adult stroke patients with unilateral upper limb involvement will be randomly allocated to three groups: (1) personalized tDCS with MRI-based electrical field simulation and optimized stimulation, (2) conventional tDCS with bihemispheric stimulation of the primary motor cortex, and (3) sham tDCS. All three groups will undergo 10 intervention sessions with 30 min of 2-mA intensity stimulation, during a regular upper limb rehabilitation program over two weeks. The primary outcome measure for the motor recovery of the upper limb impairment is the Fugl–Meyer assessment for the upper extremity score at the end of the intervention, and the secondary measures include changes in the motor evoked potentials, the frequency power and coherence of the electroencephalography, performance in activities of daily living, and adverse events with a 1-month follow-up assessment. The primary outcome will be analyzed on the intention-to-treat principle. There is a paucity of studies regarding the effectiveness of personalized and optimized tDCS that considers individual brain lesions and electrical field characteristics in the real world. No feasibility or pivotal studies have been performed in stroke patients using brain MRI, to determine a lesion-specific tDCS simulation and optimization that considers obstacles in the segmentation and analysis of the affected brain tissue, such as ischemic and hemorrhagic lesions. This trial will contribute to addressing the effectiveness and safety of personalized tDCS, using brain MRI-based electrical field simulation and optimization, to enhance the motor recovery of the upper limbs in patients with stroke.

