### 2.9. Secondary Outcomes

The secondary outcomes include the changes in the motor evoked potentials (MEPs); frequency power and coherence of electroencephalography (EEG); upper extremity functions; Wolf motor function test (WMFT) [29,30], box and block test (BBT) [31], performance in activities of daily living (ADLs) [32], and adverse events with the 1-month follow-up assessment (for details, see Table 1).

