### 2.12. Safety, Protocol, and Data Monitoring

The potential tDCS adverse events and side effects that may occur to the participants during the treatments are identified during stimulation as well as up to 30 min after the end of stimulation. If adverse events occur, they will be diagnosed by a study physician and will be reported to IRBs, according to the criteria of severity (mild, moderate, and severe). If the events are severe, the investigators must report that to the Korean Ministry of Food and Drug Safety, which will advise whether to continue, modify or stop the intervention and decide whether to unmask the group assignment.

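### Section 2.11 assigns the safety analysis to two different populations, and the per-protocol version could lose patients who stopped because of harm

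*Protocol article*

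**What the plan says.** Two sentences in section 2.11 (Statistical Analyses) fix the safety population.

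- Second paragraph: "the safety outcomes will be analyzed in the per-protocol population".
- Third paragraph: the analysis is divided into "a safety set (SS) group, a full analysis set (FAS) group, and a per-protocol set (PP) group", and then "The safety assessment will be carried out in the SS group".

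The article defines none of the three sets. The Abstract names safety, beside effectiveness, as something the trial will address.

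Adverse-event collection is described in four places.

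- Section 2.12 says that events occurring during the treatments "are identified during stimulation as well as up to 30 min after the end of stimulation".
- The Abstract lists, as a secondary measure, "adverse events with a 1-month follow-up assessment". Section 2.9 says the same and refers to Table 1 for details.
- Table 1 marks adverse events at every visit from V2 to V23. These include V12 and V23, where no stimulation is marked.
- Section 2.6.1 offers two further weeks of treatment to the two active groups but not to the sham group.

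**The concern.** The two sentences in section 2.11 give incompatible instructions. Whoever writes or applies the detailed analysis plan could cite either one. If the choice is left until the data have been seen, it becomes a post hoc decision about harms.

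The choice matters because a per-protocol set normally keeps only patients who completed treatment as planned. A patient who stops because of intolerance is then removed together with the event that caused the stop. A safety set keeps that patient. With 14 patients per arm, one removal can decide whether an event appears in the results at all.

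A second, smaller matter is the comparability of the arms. Active patients who enter the extension receive more stimulation and have adverse events recorded during it, with no sham group under the same conditions. If extension events are pooled with the rest, the arms are not compared over the same period. Table 1 also labels no visit as the 1-month follow-up.

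**Working it through.** **1. The safety population.** The third paragraph of section 2.11 names the safety set and the per-protocol set side by side as different sets, so the two sentences cannot be two names for one population. No wording limits either sentence to a sensitivity analysis. The contradiction follows from the text and needs no calculation.

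**2. What the choice could change.** The plan states no figure for safety to reproduce. The inputs for an illustration are:

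- Total sample: 42 (section 2.10).
- Allocation: 1:1:1 (section 2.5), so 42 / 3 = 14 per arm.
- Planned dropout: 10% per group (section 2.10), so 0.10 × 14 = 1.4, or 1 to 2 patients per arm.

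Two assumptions are added. First, the per-protocol set excludes patients who stopped treatment. Second, each excluded patient stopped because of the event being counted. Dropout and per-protocol exclusion need not be equal; the planned 10% is used only to choose a plausible number of exclusions.

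With *a* patients having the event in an arm of 14 and *k* of them excluded, the safety-set rate is *a*/14 and the per-protocol rate is (*a* − *k*)/(14 − *k*).

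| Patients with event, *a* | Excluded, *k* | Safety set | Per-protocol set |
|---|---|---|---|
| 1 | 1 | 1/14 = 7.1% | 0/13 = 0% |
| 2 | 1 | 2/14 = 14.3% | 1/13 = 7.7% |
| 2 | 2 | 2/14 = 14.3% | 0/12 = 0% |
| 3 | 1 | 3/14 = 21.4% | 2/13 = 15.4% |
| 3 | 2 | 3/14 = 21.4% | 1/12 = 8.3% |

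**3. The observation period.** Table 1 marks stimulation at V2, V3 to V6 and V7 to V11, which is 1 + 4 + 5 = 10 sessions, as planned. V12 is the outcome visit that follows. V13 to V17 and V18 to V22 are the extension (5 + 5 = 10 visits), and V23 is the outcome visit after it. V12 is therefore the last visit before the arms can differ in length of treatment. Section 2.6.1 closes the extension to sham, so no sham stimulation runs alongside the active extension.

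**4. The 1-month follow-up.** The only assessment after V12 outside the extension sessions is V23. It stands under the extended intervention in Table 1, and no column is labelled as 1 month. The shown text does not say whether sham patients, or active patients who decline the extension, attend V23.

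**The case against.** The strongest reply is that the paragraph devoted to analysis sets assigns safety to the safety set, so the per-protocol sentence may be a slip that would never be followed. That makes the bias conditional. It does not remove the contradiction, because both sentences are stated as rules.

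It can also be said that the per-protocol set is undefined here and that its definition may properly sit in the full protocol or the analysis plan. That stands, and it is why the table above is only an illustration. A reader might cite the device rule, "If an impedance above 13 kOhm occurs, the stimulation is stopped", as proof that harmed patients leave the set. It is not proof: the rule interrupts stimulation so that the patient's condition and skin can be checked, and it says nothing about withdrawal or exclusion. Nor do the documents show that any loss would fall mainly on the active arms.

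A reader might further infer from section 2.12 that adverse events are detected only up to 30 minutes after stimulation, so that later harms are missed. The documents do not support this. Section 2.12 describes monitoring around each session, Table 1 records adverse events at every visit after screening, and section 2.9 and the Abstract add a 1-month follow-up.

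On follow-up, V23 may itself be the 1-month assessment. Two weeks plus two weeks places it about 4 weeks from baseline, and section 2.11 analyses secondary outcomes at 4 weeks. No passage says that sham patients miss V23, and the study-design figure is not shown. Unequal follow-up is therefore not established. What stands is that the text does not say which visit serves these patients.

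**Conclusion.** Section 2.11 is wrong as written: it gives two incompatible safety populations, and one must go. This conclusion rests on the text alone.

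The consequence is conditional. It arises if the per-protocol sentence is followed, if that set excludes patients who stopped, and if some of them stopped because of an event. On those assumptions, one exclusion in an arm of 14 takes an observed rate from 7.1% to 0%, and two exclusions can take it from 14.3% to 0%. The documents do not show how often this would happen.

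The points on the extension period and the 1-month visit are smaller. The first follows from the extension being closed to sham. The second is a lack of clarity between sections 2.9 and 2.12 and Table 1, and does not show that follow-up is missing or cut off at 30 minutes.

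**What to change.** 1. In section 2.11, delete the sentence that places safety outcomes in the per-protocol population. Keep the safety set, stated as all patients with at least one stimulation, analysed by treatment received.
2. Compare the three arms on adverse events up to V12, and report extension-period events separately and descriptively.
3. Align sections 2.9 and 2.12 and Table 1. State which visit gives the 1-month adverse-event follow-up for sham patients and for active patients who decline the extension, and say in section 2.12 that session monitoring is additional to the recording at visits in Table 1.

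The first two changes are wording only. They need no extra patients, visits or data, and should be made before outcome data are examined by arm. The third is also wording only if an existing visit already serves these patients. The documents do not show whether one does, so the sponsor should confirm this first.

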### 2.10. Sample Size Estimates

Most studies that aimed to assess the efficacy of the MRI-driven optimized tDCS, were retrospective computational studies or case reports [26]. Moreover, this trial is the first to report the efficacy of the optimized tDCS on the upper limb functions in stroke patients. Considering that there were no prior data on the effects of the optimized tDCS, using an MRI-driven tDCS-induced electrical field calculation simulation on stroke patients, we estimated that enrolling 42 patients, considering a dropout rate of 10% for each group, would be a reasonable approach for an exploratory trial.

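### Section 2.11 names two different main populations for the primary efficacy analysis, intention-to-treat and per-protocol, and does not say which one decides

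*Protocol article*

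**What the plan says.** The Abstract states: "The primary outcome will be analyzed on the intention-to-treat principle". The second paragraph of section 2.11 repeats this: "The primary outcome will be analyzed in the intention-to-treat population". The third paragraph of section 2.11 introduces three analysis sets ("largely divided into a safety set (SS) group, a full analysis set (FAS) group, and a per-protocol set (PP) group") and continues: "The efficacy evaluation will analyze the PP group as the main analysis group and analyze the FAS group".

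For disagreement between the sets, it says: "If the results are different across the analysis groups, the results of each analysis method will be presented and analyzed to identify the reason".

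The primary outcome is the change in FMA-UE from baseline to 2 weeks (section 2.8). This is an efficacy outcome, so the sentences on the primary outcome and on the efficacy evaluation both govern it.

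**The concern.** The two instructions cannot both be followed for the same endpoint. An analyst working from paragraph 2 would report the intention-to-treat result as primary. An analyst working from paragraph 3 would report the PP result. The plan promises both results but does not say on which one the conclusion rests.

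The choice matters because of the trial's question. The Introduction hypothesises that optimised stimulation is better than conventional stimulation, and a sham arm is included, so this is a superiority comparison. A PP set is formed from what happens after randomisation. If the reasons for exclusion relate both to arm and to outcome, the remaining groups are no longer comparable. With 14 patients per arm, one or two exclusions can move the estimate noticeably.

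**Working it through.** **1. The statements side by side**

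| Place | Population for primary efficacy |
|---|---|
| Abstract | intention-to-treat |
| 2.11, paragraph 2 | intention-to-treat |
| 2.11, paragraph 3 | PP as main, FAS in addition |
| 2.11, rule if the sets differ | present both; no precedence |

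The same two paragraphs also disagree on safety. Paragraph 2 reads "The primary outcome will be analyzed in the intention-to-treat population, and the safety outcomes will be analyzed in the per-protocol population", and paragraph 3 reads "The safety assessment will be carried out in the SS group, and the significance level will be set at 0.05". That is a separate point, but it shows that the paragraphs were not reconciled, so a reader cannot infer which one prevails.

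**2. Inputs for an illustration**

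- Enrolment is 42, allocated 1:1:1 (sections 2.5 and 2.10): 42 / 3 = 14 per arm.
- Dropout is 10% for each group (section 2.10): 14 × 0.9 = 12.6, a loss of 1.4, so 1 to 2 patients per arm. Treating this as the loss from PP is an assumption.
- The significance level is 0.05 (section 2.11); two-sided tests are assumed.
- The plan has no power figure to reproduce. Section 2.10 says only that "we estimated that enrolling 42 patients, considering a dropout rate of 10% for each group, would be a reasonable approach for an exploratory trial". An assumed 12 evaluable per arm gives 12 / 0.9 = 13.3, rounded up to 14, and 3 × 14 = 42. This is consistent with the plan, but the 12 is not in it.

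**3. Size of a spurious difference under no true effect**

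Assume normal outcomes with unit SD. Two of 14 patients are lost from one active arm and none elsewhere. They are the two lowest on an exclusion score s = ρx + √(1 − ρ²)e, where x is the outcome, e is independent noise and ρ is the loss-outcome correlation.

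The two lowest of 14 standard normal values have expectations of about −1.70 and −1.21. The mean of the 12 who remain therefore rises by

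shift = ρ × (1.70 + 1.21) / 12 = ρ × 0.24.

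This gives 0.12 SD at ρ = 0.5 and 0.24 SD at ρ = 1.0. Simulation gives the same values.

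**4. Type I error in that scenario, simulated at nominal 5%**

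| Test on the reduced set | ρ = 0.5 | ρ = 1.0 |
|---|---|---|
| Three-group test | 6.1% | 9.9% |
| Two-arm t-test, no gate | 6.2% | 10.8% |
| Pairwise claim only after a significant three-group test | 3.2% | 5.9% |

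The third row follows the sequence in section 2.11, where pairwise comparisons come only after a significant three-group result. Repeat runs move these figures by a few tenths of a percentage point at most. One-way tests stand in for the planned repeated measures ANCOVA.

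**5. Reading significance from either set when loss is purely random**

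With 1 to 2 patients lost per arm, the chance that at least one set is significant under the null is about 6.4% to 6.7% in a two-arm test, and 6.4% (one lost) or 7.0% (two lost) in the three-group test. With one pre-named full randomised set it stays at about 5%.

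**The case against.** The strongest reply has four parts.

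- **Both results are promised.** Section 2.11 commits to analysing both sets and to presenting both if they differ. A reader might infer that the sponsor could quietly pick the favourable set after seeing the data. The documents do not support that: the pledge limits hidden selection. It still does not say which result carries the conclusion.
- **The trial is small and exploratory.** Section 2.1 calls it a phase 2 feasibility study and section 2.10 calls it exploratory, so a PP-led reading does less harm than in a confirmatory trial. This lowers the stakes. However, section 2.11 also seeks statistically significant differences and section 3 aims to prove benefit, and the label does not decide which population is primary.
- **The cause and number of exclusions are not given.** A reader might infer that patients whose stimulation was stopped for skin or impedance reasons would leave the PP set, and would do so more often under active stimulation. Section 2.6.1 describes stopping above an impedance limit but does not make it a PP exclusion. Nor is dropout the same as PP exclusion: a patient without a 2-week FMA-UE is also missing from an observed-case FAS. Both steps are assumptions.
- **The larger error rates are extreme.** A reader might take nearly 11% as the plan's false-positive risk. That figure needs loss perfectly tied to outcome, all in one active arm, and a pairwise test without the planned gate. With two lost from each arm by the same mechanism, the ungated test gives 5.6% to 8.5%. With one lost from one arm only, it gives 5.4% to 7.1%.

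None of this removes the contradiction. Condensation into an article and an unseen analysis plan do not explain it either, because nothing is said to be missing: two statements in one section conflict.

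**Conclusion.** The contradiction stands on the text alone and should be corrected. Intention-to-treat and PP are both assigned to the primary efficacy result of a superiority comparison, with no rule on which prevails.

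The numerical consequence is uncertain. A PP-led result can be biased, but the documents do not allow the size or direction to be stated. Under the one-arm loss assumed above, the inflation is modest for the three-group test (about 6% to 10%). A pairwise claim behind the gate stays at about 3% to 6%, although the gate itself holds that rate below 5% when nobody is lost, so 5% is a lenient benchmark there. The stronger inference, that the plan as written yields a broken comparison or a known false-positive rate near 11%, is not supported.

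**What to change.** In the third paragraph of section 2.11, delete the clause that makes PP the main analysis group. In its place state that:

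- the primary FMA-UE analysis uses the ITT/FAS population, defined as all randomised patients analysed in the arm to which they were allocated;
- the PP analysis is supportive only;
- if the two differ, both are reported and the conclusion follows the FAS.

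This agrees with the Abstract and the second paragraph of section 2.11. It also settles that the intention-to-treat population of paragraph 2 and the FAS of paragraph 3 are the same set. The cost is a sentence or two, with no new data and no change to the sample size. It should be done before treatment codes are opened.
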